## Abstract

**Background:**

Neoadjuvant systemic therapy is offered to selected women with large and/or highly proliferative operable breast cancers. This option adds further complexity to an already complex breast cancer treatment decision tree. Patient decision aids are an established method of increasing patient involvement and knowledge while decreasing decisional conflict. There is currently no decision aid available for women considering neoadjuvant systemic therapy.

**Objective:**

We aimed to develop a decision aid for women diagnosed with operable breast cancer and considered suitable for neoadjuvant systemic therapy, and the protocol for a multicenter pre-post study evaluating the acceptability and feasibility of the decision aid.

**Methods:**

The decision aid was developed through literature review, expert advisory panel, adherence to the International Patient Decision Aid Standards, and iterative review. The protocol for evaluation of the decision aid consists of the following: eligible women will undertake a series of questionnaires prior to and after using the decision aid. The primary endpoint is decision aid acceptability to patients and investigators and the feasibility of use. Secondary endpoints include change in decisional conflict, participant knowledge, and information involvement preference. Feasibility is defined as the proportion of eligible participants who use the decision aid to help inform their treatment decision.

**Results:**

This study has recruited 29 out of a planned 50 participants at four Australian sites. A 12-month recruitment period is expected with a further 12-months follow-up.

**Conclusions:**

The decision aid has the potential to allow patients with operable breast cancer, who have been offered neoadjuvant systemic therapy, decreased decisional conflict, and greater involvement in the decision. If this study finds that an online decision aid is feasible and acceptable, it will be made widely available for routine clinical practice.

**Trial Registration:**

Australian and New Zealand Clinical Trials Registry ACTRN12614001267640; http://www.anzctr.org.au/TrialSearch.aspx?searchTxt=ACTRN12614001267640&isBasic=True (Archived by WebCite at http://www.webcitation.org/6gh7BPZdG)

## Introduction

Neoadjuvant systemic therapy (NAST) has become a routine treatment option for selected women with operable breast cancer, endorsed by international guidelines [1, 2], patients [3], doctors [4], and breast cancer advocates [5]. We estimate that at least 20% of patients with breast cancer might benefit from NAST; however, this rate varies among clinicians [6]. It has the advantages of down-staging some larger tumors from mastectomy to lumpectomy [7], providing prognostic information depending on the degree of tumor response [8], and facilitating translational research for early biomarkers of response [9]. In tumors with higher rates of proliferation such as triple negative and HER2 (human epidermal growth factor receptor 2)-positive, pathological complete response is considered a surrogate outcome for the approval of novel therapies [10]. Additional potential benefits include additional time for surgical decision making, genetic testing, and downstaging of the axilla [11]. Overall survival and disease-free survival are equivalent following either neoadjuvant or adjuvant systemic therapy with appropriate local therapy [12]. Despite these advantages, NAST is not frequently used for women with operable disease, with one Australian study reporting an estimated rate of 2.75% [4], and in the United States 3.8% [13]. Possible reasons for this low rate of NAST use include the need for changes in workflow practices, patient expectation for upfront surgery, patient lack of awareness of NAST, and lack of available clinical trials [6]. Potential disadvantages to NAST include the loss of detailed pathology to guide multidisciplinary management; the (low) potential to delay surgery in patients who do not respond to NAST; and reduced time between surgery and radiotherapy, which may impact on breast reconstruction outcomes [4].

In a series of semistructured interviews conducted by our group, women with breast cancer expressed interest in NAST, for down-staging, prognostication, and to allow additional time to plan surgery [3]. However, they were not able to be as involved as they would like in the decision to receive NAST rather than adjuvant systemic therapy. They reported a lack of information, meaning that they did not feel adequately informed about the options available. They felt that clinicians tended to direct them toward one option, rather than their preference of shared control. This skewed distribution of decisional control was echoed in a survey of 207 Australian and New Zealand breast cancer specialists, where the majority of clinicians directed the decision about whether NAST would be given for operable breast cancer. This study, using an adaptation of the Control Preferences Scale [14], found that no clinicians reported that their patients made the final decision about NAST [15]. This indicates a mismatch between patient wishes and the experience of shared decision making [16], and suggests that strategies are required to better involve patients in the decision about NAST.

Women with early stage breast cancer typically desire involvement [17] and decisional control over their treatment [18]. Those who are at least as involved as they wanted experience better decision-related outcomes including consultation satisfaction, satisfaction with decision making, perception of clinician-shared decision-making skills, and decreased decisional conflict [18]. Being involved in decision making about breast cancer is associated with improved quality of life up to 10 years postdiagnosis [19]. However, it may be particularly difficult to engage women in decisions about NAST due to the complexity of the decision, distress from breast cancer diagnosis, perceived urgency, and an expectation that surgery will be the first treatment offered [3]. Patients may also want to proceed with up-front curative surgery in the hope that chemotherapy, which is seen as toxic and intrusive [20], may be avoided entirely.

Patient decision aids (DA) are an established method to improve the quality of shared decision making. Patient decision aids for treatment decisions have been shown to decrease decisional conflict, increase knowledge about options, improve risk perception, and improve patient-practitioner communication [21]. Decision aids are particularly suited to decisions where the various risks and benefits of the alternative treatment options may be valued differently by different individuals [22]. The choice between NAST and conventional sequencing (surgery followed by chemotherapy) is such a decision. In a systematic review of decision aids for patients with early stage breast cancer, we could not find any reports of a decision aid for NAST [23]. In our Australian survey, 86% of breast cancer specialists expressed interest in using a decision aid for women with operable breast cancer who are offered NAST. Women who were interviewed endorsed the development of a NAST DA and expressed a preference for a tool in print form that was accessible from a trusted source. In this paper, we describe the development of such a DA and the protocol for a study that will evaluate that DA.

## Methods

### Decision Aid Development

A DA (see Multimedia Appendix 1) was developed based on a literature review and then refined in an iterative process by an expert advisory panel comprising medical oncologists, breast surgeons, a psycho-oncologist, consumers, a breast care nurse, and a breast cancer advocacy organization representative according to the systematic process described by Coulter et al [24]. A skilled consumer advocate with personal experience of breast cancer reviewed the decision aid on multiple occasions and provided constructive advice. The structure of the DA was based on the International Patient Decision Aid Standards Collaboration statement, to include a balanced description of adjuvant and neoadjuvant therapy, including advantages and disadvantages, outcome probabilities for each option, graphics, and a values clarification exercise. The DA was then circulated to an additional stakeholder group with similar composition to the first, who had not seen the DA, for further refinement. It was then professionally formatted in portable document format (.pdf) to be downloadable and printable in either color or black and white.

The final DA includes an introduction, brief general information about breast cancer and the treatments used, explanation of the options for the timing of chemotherapy and surgery, the advantages and disadvantages of neoadjuvant and adjuvant therapy, a values clarification exercise, a page for notes, a glossary, and information about where to find additional resources. Using the readability statistics package embedded in Microsoft Word, the decision aid has a grade 10 Flesch-Kincaid readability level. The introduction is necessary for newly diagnosed breast cancer patients to understand basic concepts about treatment modalities because they may not have received other written general information at the time that NAST is being discussed. A diagram represents the options of either chemotherapy followed by surgery or surgery followed by chemotherapy. Radiotherapy (if indicated), HER2-directed therapy (if HER2 positive), and endocrine therapy (if estrogen [ER] and/or progesterone receptor [PR] positive) follow in the flow diagram in Multimedia Appendix 1. The diagram is designed to demonstrate that treatment duration is expected to be similar with either option.

Key components of risk are presented using visual, numeric, and narrative formats with appropriate labeling, tailored to individual tumor characteristics [25]. The likelihood of a pathological complete response is presented according to breast cancer subtype: ER/PR (hormone receptor [HR]) positive, HER2 negative; HR positive, HER2 positive; HR negative, HER2 positive; and HR negative and HER2 negative (triple negative [TNBC]). The probability of remaining alive and free of breast cancer at 5 years is presented, based on whether a pathological complete response was achieved, or not. These estimates are based on a meta-analysis of neoadjuvant clinical trial results reported by von Minckwitz et al [26] and Cortazar et al [8]. A 1000-dot diagram, with each dot representing one patient, illustrates the likelihood of tumor progression (3%) or becoming inoperable (0.3%) on neoadjuvant chemotherapy, based on a case series by Caudle et al [27].

The values clarification exercise in this DA is a diagram with statements about advantages and disadvantages of either option [28]. Patients can nominate how important each factor is to them and then make a mark on a linear analogue scale to show which option they prefer and how strong their view is. Patients are encouraged to discuss their options with friends, family, and other health professionals if they wish. The final decision is made at a follow-up visit with their surgeon or medical oncologist.

**Figure 1 figure1:**
[figure not shown]
Study schema.

### Evaluation of Decision Aid

ANZ1301 is a multicenter study using a pre-post design to evaluate the acceptability and feasibility of the decision aid (Figure 1) described above. The project is being led by the Australia and New Zealand Breast Cancer Trials Group (ANZBCTG) in collaboration with the Psycho-oncology Co-operative Research Group. It is funded by an HCF Research Foundation grant with central trial coordination by the ANZBCTG. All four sites have received ethics approval from the Hunter New England Local Health District Human Research Ethics Committee, under the Australian National Mutual Acceptance multicenter ethics scheme.

### Study Participants

#### Clinicians

In total, 26 clinicians from four ANZBCTG sites have been recruited to identify women eligible for the DOMINO (DecisiOn MakIng about NeOadjuvant) study. Participating sites are Calvary Mater Newcastle, Waratah, NSW; The Breast and Endocrine Center, Gateshead, NSW; The Mater Hospital, North Sydney, NSW; and Royal Melbourne Hospital, Parkville, VIC. Patients are screened at those four sites and in the private practices of associated clinicians. All participating clinicians and site study personnel receive training on the online system developed for this study.

#### Patients

Patients are eligible to participate in the DOMINO study if they are female and aged over 18 years; have a histological diagnosis of invasive breast cancer; have an operable invasive breast tumour; are considered appropriate for neoadjuvant systemic therapy (NAST) with curative intent using chemo- and/ or endocrine therapy; are able and agree to access study information via the Internet; are able to comply with the study procedures for the duration of the study; and give voluntary, informed consent.

Patients are ineligible if they are expected to receive fewer than 3 months of NAST; have a hearing or other impairment that would preclude a phone interview; are unable to access the Internet using a laptop or desktop computer, or do not have an active email address with which to participate in the study; have insufficient English language skills for participation in online surveys and oral interviews; have inflammatory, metastatic, or inoperable breast cancer; or have a medical or psychiatric condition that precludes informed consent or prevents adherence to study procedures.

### Study Design

#### Screening

Potentially eligible patients are identified during the planning of their initial treatment strategy at participating Australian sites during multidisciplinary meetings and at surgical and medical oncology appointments. Patients are approached by their clinician during their appointment to consider receiving additional information about the DOMINO study via a Web link that is sent to the patient via an auto-generated email. At the time of the initial offer of study participation, patients are asked to indicate written consent on a screening form for their personal information (name, email address, and telephone number) to be provided to the ANZBCTG. A Web link to the study consent page and questionnaires is then sent to them by email. Patients who consent to share personal information are provided with a copy of their signed screening consent form along with study-specific written information about their breast cancer. This information is intended to aid understanding of their diagnosis when using the decision aid. Clinicians are required at this time to record details regarding the primary reason for NAST, as well as an opinion of the patient’s current distress levels and information preferences. The completed screening consent form is sent via Teleform (Hewlett Packard) fax to the ANZBCTG to be verified, and email contact with the patient is established.

If the patient does not consent to share personal information, the clinician records information on the screening consent form so a log can be kept of each patient who is ineligible and screened out, eligible but not offered participation, and offered participation but declines. The number of patients who consent to screening but do not participate in the study will also be recorded. Screening data will be used to describe feasibility of DA use.

#### Registration

Patients are registered to the study through the following process. The screening form is received at the ANZBCTG for validation and confirmation of eligibility criteria. Patients who consent to release their details on the screening form receive an automatically generated email. These patients are now considered eligible for the DOMINO study. Patients who access, read the online DOMINO Information Statement and Consent page, and agree to participate in the study are redirected to a series of demographic questions. On submission of responses to demographics and consent, patients are considered registered to the study. Patients at this stage are also given the opportunity to opt in to a telephone interview. Eligible patients have a 6-week window in which to view and agree to participate in the DOMINO study before being considered a screen failure. We aim to register 50 patients to the DOMINO study.

#### Electronic Communication Processes

At the point of registration, patients are requested to enter a password to access the DOMINO website. Thereafter, an individual’s username is defined by their email address.

Site trial coordinators input dates of patient appointments and projected treatment completion dates, which are then used to calculate and trigger all communication with the patient and reminders to site coordinators. Pre-designed patient and site coordinator emails are sent automatically at specific timepoints, as guided by information entered by sites as to the treatment decision (either NAST or surgery), to patients. A reminder email is sent to the patient if the survey remains unsubmitted 3 calendar days after the initial email. If after an additional 2 calendar days a patient has not submitted a questionnaire, an automatically generated email is sent to the ANZBCTG study coordinator prompting a telephone call to the patient. Site study coordination staff are sent automatically generated emails prompting completion of data via the online system or informing them of their patient’s submission of a questionnaire.

### Outcome Measures

#### Primary Outcomes

DA acceptability is the first outcome. It is defined as at least half of patients considering the DA useful for their decision and at least half of clinicians indicating that they would use the DA in their routine clinical practice. Acceptability will be assessed using a single question from the DA feedback questionnaire developed by Juraskova et al [29] about whether the patient considered the DA useful for their decision. This questionnaire also measures general satisfaction with the DA.

Feasibility of DA use will also be assessed as an outcome. We define it as at least half of patients who were offered participation in the study accessing the DA, and at least half of those who access the DA stating that they read it.

#### Secondary Hypotheses and Outcome Measures

We hypothesize that with use of the DA the Decisional Conflict Scale score will decrease [30]; knowledge about NAST, using a custom-designed questionnaire, will increase; information and involvement preference will increase [31]; agreement between preferred and achieved decision control will be high, based on an adaptation of the Control Preferences Scale to include achieved control [14]; and the Control Preferences Scale score will increase [14]. Further, there will be no change in cost of health care delivery or in the 6-item State-Trait Anxiety Inventory score [32]. Fear of cancer progression will be unchanged while receiving neoadjuvant therapy [33]; the Decisional Regret score after chemotherapy and after surgery will be low [34]; fear of cancer recurrence score will be low [35]; distress thermometer score will decrease [36, 37]; satisfaction with decision score will be high [38]; and there will be no change in outcomes between those who decided to receive neoadjuvant chemotherapy with those who decided not to have neoadjuvant therapy.

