#### Knowledge Questionnaire

A custom-designed 7-item knowledge questionnaire has been developed based on the content of the DA to test recall and comprehension (see Multimedia Appendix 2). Questions were taken from information throughout the DA. The number of correct responses will be transformed to a score out of 100.

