#### Questionnaire Administration

A series of validated questionnaires where available, and custom designed where a questionnaire is not available, are presented to patients at four timepoints before and after access to the decision aid (see Table 1). Prior to access to the decision aid, patients are asked to report demographics and to complete 6 questionnaires that address decisional conflict, decision-making preference, information and involvement preferences, anxiety, distress, and an optional health economic instrument.

At the completion and submission of the first set of questionnaires, patients are able to access an electronic copy of the decision aid. This document can be printed, saved, and accessed by a patient at any stage of the study by logging in to the DOMINO website. Patients are asked to complete and read the decision aid prior to attending their next appointment with their clinician, at which time a decision regarding treatment may be made. At this visit, the clinician refers to the decision aid and asks whether the patient has any questions about it. After the attendance at an appointment where a decision was made regarding treatment and specific data have been entered by the site, the patient receives an autogenerated email informing them that a second set of questionnaires is available for completion. Questionnaires at this timepoint ask the patient to reflect on the information provided in the DA and its role in their treatment decision. Patients who do not submit both questionnaire sets 1 and 2 will be replaced to ensure that pre-post outcomes are recorded for 50 patients.

Based on treatment details supplied by the site trial coordinator about treatment option chosen and date of completion, an email link to questionnaire set 3 is sent to the patient. This questionnaire is to be completed after the initial treatment strategy of either chemotherapy or surgery. It is expected that most participants will then proceed with surgery or systemic therapy respectively as their subsequent treatment strategy. This assessment aims to determine the effect of the first treatment strategy on decision-related outcomes, without the influence of the alternative strategy.

Questionnaire set 4 is answered 12 months after registration, to investigate longer-term outcomes including anxiety, distress, regret, and recollection of pathology results. This is the last questionnaire, and participants complete their study involvement at this time.

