**Decision-making preference questionnaire**						
	Preferred	X	X			
	Actual		X			
Distress thermometer		X	X	X	X	X
Information and involvement preferences		X	X			
EQ-5D-5L (optional)		X	X	X	X	X
Knowledge of decision aid information			X			
Decision aid feedback			X			
Satisfaction with decision scale			X			
Fear of progression (FOP 12)			X	X	X	
Decision regret scale				X	X	X
Fear of Cancer Recurrence Inventory				X	X	X
Participant-reported pathology results (NAST only)						X

^a^Postchemotherapy, before surgery.

^b^Postsurgery, before adjuvant chemotherapy.

^c^12 months (+/- 1 month) after registration.

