### Statistical Analysis

A sample size of 50 participants is planned. The primary analysis will include all registered patients and clinicians as two separate cohorts. The proportion of patients and investigators who consider the DA acceptable will be reported with 95% exact confidence limits. The primary outcome will be considered positive if more than half of patients and clinicians consider the DA acceptable, and feasible if more than half of eligible patients who are offered participation register and subsequently use the DA. Assuming a sample size of 50 participants, the primary outcome of percentage of participants finding the DA acceptable can be estimated to within ±15% based on 95% exact confidence limits. To ensure that the lower 95% one-tailed exact confidence limit is greater than 50%, at least 32 of the 50 participants will need to indicate DA acceptability. Although the study is not powered to test the secondary hypotheses, there is 80% power to detect a change of at least 0.40 standard deviations from the pre- to post-DA assessments using a two-tailed *t*-test with alpha=.05 and a sample size of 50 participants.

Changes in secondary outcome measures from the pre-DA assessment, including decisional conflict, information preference, anxiety, distress, and fear of progression, will be evaluated using repeated measures analysis of covariance (ANCOVA). All outcomes will be described using mean and standard deviation for continuous measures and frequency for categorical outcomes. If data are skewed, median and interquartile range will be reported and the appropriate linearizing transformation will be used. Analyses will be performed unadjusted and adjusted for age, level of education, information preferences, and tumor characteristics (size, grade, node involvement, ER/PR/HER2). Agreement in decisional control before and after using the DA, and between preferred and actual control, will be assessed using a weighted kappa statistic with McNemar test. Knowledge will be reported as mean proportion of items correct with standard deviation. Cost will be recorded using Australian Medical Benefits Scheme item numbers and Pharmaceutical Benefits Scheme prices, and a comparison made between those who receive surgery first and those who receive systemic therapy first.

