## Discussion

### Principal Considerations

This study intends to evaluate the acceptability and feasibility of a DA for women with operable breast cancer who have been offered NAST. It is designed as a single arm pre-post study to allow all participants access to the intervention. The population of Australian women who currently receives NAST is relatively small, limiting the feasibility of a larger, randomized controlled trial with comparative outcomes. However, the proportion of patients receiving NAST in Australia and New Zealand is expected to increase as a result of increased awareness, availability of neoadjuvant clinical trials, and from the results of ongoing neoadjuvant and post-neoadjuvant trials.

The study primary endpoints are pragmatic. We expect that some participants will not find the DA beneficial, based on their decision-making style and information-seeking behavior. However, we hypothesize that the number who find it helpful in their decision-making process will be greater than the number who do not find it useful. Because DAs have variable use across centers and individual clinicians [40], feasibility was included as an endpoint. A screening log is designed to quantify the number of patients who are seen at recruiting sites who are candidates for NAST for operable breast cancer; are eligible for the study; are offered study participation; accept study participation; and go on to access the DA. This will identify the proportion of eligible patients who are not offered participation (clinician feasibility) and the proportion of eligible patients who do not access the DA after being offered it (patient feasibility). Acceptability will be assessed using direct questions to patients and clinicians.

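### Knowledge is hypothesised to increase with use of the decision aid, but it is scheduled once, after the decision, in a single-arm study, so no increase can be estimated.

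*Protocol article*

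**What the plan says.** The protocol article, under Secondary Hypotheses and Outcome Measures, lists what is expected with use of the DA, including that "knowledge about NAST, using a custom-designed questionnaire, will increase". The Knowledge Questionnaire section describes the instrument: "A custom-designed 7-item knowledge questionnaire has been developed based on the content of the DA to test recall and comprehension". It is scored out of 100.

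The schedule appears twice. In Table 1 the row "Knowledge of decision aid information" has one mark, at the posttreatment decision assessment. Questionnaire Administration says that, before access to the DA, patients report demographics and "complete 6 questionnaires that address decisional conflict, decision-making preference, information and involvement preferences, anxiety, distress, and an optional health economic instrument". Knowledge is not among these six.

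On design, the Discussion (Principal Considerations) says: "It is designed as a single arm pre-post study to allow all participants access to the intervention".

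On analysis, the Statistical Analysis section says: "Knowledge will be reported as mean proportion of items correct with standard deviation". The outcomes to be analysed for change are introduced separately: "Changes in secondary outcome measures from the pre-DA assessment, including decisional conflict, information preference, anxiety, distress, and fear of progression". Knowledge is not named there. The same section states 80% power for a pre-to-post change of 0.40 SD with 50 participants.

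The abstract (Methods) words the endpoints as follows: "Secondary endpoints include change in decisional conflict, participant knowledge, and information involvement preference".

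**The concern.** An increase is a comparison, and the protocol gives nothing to compare with. It schedules no baseline score, has no concurrent control, and states no historical or threshold value.

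The quiz items are drawn from the DA. They are answered after the patient has had the DA and after an appointment at which the clinician refers to it and invites questions. A high score could reflect the DA, that consultation, what the patient already knew, or easy items. One score per patient cannot separate these.

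What is at stake is the reporting. The Conclusion names greater knowledge as a potential benefit of the DA, and the Discussion holds that a randomised trial is not needed before dissemination. A good post-decision score set beside a hypothesis of increase could easily be read as evidence of a gain that was never measured.

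**Working it through.** **1. Measurements available for knowledge** (Table 1, checked against Questionnaire Administration)

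| Assessment | Knowledge scheduled? |
|---|---|
| Pre-DA | No |
| Post treatment decision | Yes |
| Post chemotherapy / post surgery | No |
| 12 months after registration | No |

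The gap is not an effect of broken table layout. Other rows, such as the distress thermometer, carry a pre-DA mark one column earlier than the only knowledge mark, and the prose list of six pre-DA questionnaires independently omits knowledge. Planned pre-DA scores: 0 of 50. Planned within-patient differences: 0 of 50.

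**2. The protocol's own pre-post power figure**

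Inputs, from Statistical Analysis: n = 50, change 0.40 SD, two-sided alpha 0.05, stated power 80%.

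- Noncentrality = 0.40 × √50 = 2.83, with 49 degrees of freedom.
- Power of the paired t-test (noncentral t) = 79.2%.
- Normal approximation: Φ(2.83 − 1.96) = Φ(0.87) = 80.7%.
- Change detectable at exactly 80% power (noncentral t) = 0.404 SD.

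The stated figure is reproduced. It stands for outcomes measured both before and after the DA. It needs two measurements per patient, so it cannot apply to knowledge, which has one.

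**3. What a single post-decision score supports**

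Half-width of the 95% confidence interval for a mean, in SD units = t(0.975; 49) / √50 = 2.01 / 7.07 = 0.28.

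This assumes that all 50 give a usable score. The protocol gives no SD for the score, so the half-width cannot be put on the 0 to 100 scale.

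**4. If a pre-DA quiz were added during recruitment**

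Results reports 29 of 50 registered as of February 2016, leaving 50 − 29 = 21. The number who would contribute a pair is an assumption. The change detectable with 80% power (paired t-test, two-sided 5%) is:

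| Pairs assumed | Detectable change |
|---|---|
| 21 | 0.64 SD |
| 25 | 0.58 SD |

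**The case against.** The best case for the protocol is that its analysis section already treats knowledge correctly. A descriptive mean and SD fits a single measurement, and no section plans a test or an estimate of change in knowledge. Knowledge is also secondary, the protocol says that the study is not powered for secondary hypotheses, and neither acceptability nor feasibility depends on it. All of this stands. It limits the consequence and shows that the hypothesis is the part out of line. It does not make a directional hypothesis answerable without a comparison value.

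Two stronger readings are tempting and should not be made.

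- A reader might infer from the abstract that knowledge is formally a change endpoint. The words can equally be read with the change applying to decisional conflict alone, and the analysis section does not name knowledge among the change outcomes, although that list is open-ended. The point rests on the stated hypothesis, not on the abstract.
- A reader might take 21 as the most that could still give a baseline. The protocol does not establish this. Patients who do not submit both of the first two questionnaire sets are replaced, so later registrations may exceed 21. Registration precedes the first questionnaire set, so some of the 29 may not yet have reached the DA. The count is also a dated snapshot, and the number could be lower.

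A further objection is that adding a pre-test part-way would have some participants take the quiz twice and others once, which could disturb the one knowledge result the plan does support. That is a real cost and is carried into the fix.

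**Conclusion.** The concern holds as a mismatch between a stated hypothesis on one side and the schedule, design and analysis on the other. With 0 of 50 planned participants having a scheduled pre-DA score and no comparator, an increase in knowledge cannot be estimated or attributed to the DA. The 0.40 SD power statement is arithmetically sound but does not extend to this outcome. The study can deliver a post-decision mean to within about 0.28 SD, given 50 usable scores.

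The finding does not mean that the protocol plans an invalid test of knowledge change, and it does not touch the primary outcomes. It is a matter of what may be concluded about one secondary outcome, and should be corrected before results are reported.

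**What to change.** 1. In Secondary Hypotheses and Outcome Measures, replace the expected increase with a descriptive aim: the post-decision knowledge score.
2. In Statistical Analysis, add a 95% confidence interval to the planned mean and SD, and make clear that the pre-post power statement does not cover knowledge.
3. Reword the abstract's endpoint sentence so that the change cannot be read as covering knowledge.
4. Make no claim in the report that the DA increased knowledge.

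These are wording changes with no cost in data.

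Optionally, the existing 7 items could be added to the first questionnaire set for participants who have not yet accessed the DA. This needs a small change to the online form and notice to the ethics committee, takes participants a few minutes, and may prime them for the DA content. If it is done, report the paired change as exploratory only, report post-DA scores separately for those with and without the pre-test, and state the number contributing as an assumption (for example, 21 pairs give 80% power for about 0.64 SD), not as a maximum.
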